### 2.6. Study-Specific Visits and Procedures

Table 1 shows the study-related procedures. All eligible patients should have a 2-week run-in period followed by the treatment period. Participants are assessed by the same researcher consistently throughout the trial. Baseline measures include demographic data; medical and treatment history; medications; vital signs (temperature, breathing, heart rate, and blood pressure); FBG, 2hPDG, HbA1c, and TG levels; and liver and kidney function tests. Baseline measurements will be repeated with all participants at T1 and T4. The TCM syndrome indicators, SAQ, adverse events, and outcome measures will be recorded from T1 to T4.

### 2.7. Randomization and Blinding

Eligible patients are randomly allocated to the treatment or control group in a 1 : 1 ratio. The randomization sequence will be recorded by staff at the sponsor unit. The researchers and outcome assessors participating in this study have no knowledge of the randomization sequence details. In addition, the results are kept in sealed, opaque, and stapled envelopes. They will be unsealed at the end of the outcome assessment. Emergency letters, including random codes and group assignments, are prepared by a statistician. If the blind code is exposed, patients will be excluded accordingly. Any of the following situations could call for a blind breaking and urgent measure: a serious adverse event, serious complication, or a deterioration in the patient's condition.

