### 2.3. Intervention

Patients who meet all the inclusion and none of the exclusion criteria will be randomized into two groups as follows: (1) treatment group, 0.5 g of Zhenyuan capsule, 3 times/day, and (2) control group, 0.5 g of placebo, 3 times/day. According to the Guideline for the Diagnosis and Treatment of Chronic Stable Angina, participants can maintain the conventional drug treatments such as antiplatelet agents, statins, nitrates, anticoagulation drugs, *β*-blockers, calcium channel antagonists, angiotensin-converting enzyme inhibitors, or angiotensin II receptor antagonists. However, statins are the only Western medicine for lipid treatment. Patients diagnosed as having type 2 diabetes maintain the current Western medicines for hypoglycemic effects. To avoid discussing their medications among themselves, participants are advised to take the drugs at home and required to remain isolated from each other. In addition, the treatment allocation remains blind throughout the study. Participants will not be permitted to use other treatments for angina pectoris in CHD and diabetes, including TCM herbs and Chinese patent medicine. In the run-in period, any TCM medications for improving blood lipid or glucose levels will not be permitted.

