### 2.8. Data Entry and Quality Control

The data of the participants collected according to the Case Report Forms will be imported into the clinical data management system (http://www.xyedc.com/). To keep the data consistency, the supervisor will compare the electronic database with the source documents and correct any identified errors. In addition, computer logic checks will be run after data entry. Manual checks and the Data Coordination Center will also help to identify more complicated and less common errors. All these measures are used to ensure the accuracy and integrity of information.

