### 2.10. Statistical Analyses

Statistical analyses will be conducted by an independent statistician from Xiyuan Hospital. In the FAS, patients will be dosed with the study drugs at least one time and one clinical observation will be recorded. Participants with good compliance and without any protocol deviations will be included in the per-protocol set (PPS). Subjects with safety data who have completed at least one study visit will be included in the safety analysis. The mean ± SD will be used in continuous variables. The characteristic comparability between the two groups will be evaluated by a two-sample Student *t*-test for continuous variables and the Fisher exact test or *χ*^2^ test for categorical variables. In this multicenter trial, the Cochran-Mantel-Haenszel test and the analysis of variance will be used. For diminishing the influence of confounding factors on the curative effect, analysis of covariance and the logistic regression model will be applied. For all the analyses, the difference with a value of *P* < 0.05 will be statistically significant. All analyses will be conducted using the SAS software version 9.3 (SAS Institute, Cary, NC, USA).

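### The allocation is unsealed at the end of outcome assessment rather than at database lock, so final data correction and per-protocol selection may be done with treatment known

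*Protocol article*

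**What the plan says.** Section 2.7 (Randomization and Blinding) states that "the results are kept in sealed, opaque, and stapled envelopes" and then gives the event that opens them: "They will be unsealed at the end of the outcome assessment". It describes who is kept blind in these terms: "The researchers and outcome assessors participating in this study have no knowledge of the randomization sequence details". Emergency letters for individual patients are a separate mechanism with their own triggers.

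Section 2.8 (Data Entry and Quality Control) says that "the supervisor will compare the electronic database with the source documents and correct any identified errors". It continues: "In addition, computer logic checks will be run after data entry". Manual checks and a data coordination centre follow. The section does not place any of these steps before the unsealing.

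Section 2.10 (Statistical Analyses) defines the per-protocol set: "Participants with good compliance and without any protocol deviations will be included in the per-protocol set (PPS"). It gives no compliance threshold and does not say when, or by whom, membership is decided. Table 1 schedules drug return and counting at weeks 4, 8 and 12.

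Section 2.3 (Intervention) adds that "the treatment allocation remains blind throughout the study", directly after a passage on keeping participants from comparing their medication.

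**The concern.** In a double-blind trial the blind has to last until the data are final and each analysis set is fixed, not only until the last measurement is taken. Between those two points people still make decisions: which discrepancies to correct, which departures count as deviations, and whose compliance was good enough. Section 2.7 ties the end of the blind to the last measurement. Anyone following that sentence as written could open the envelopes while these decisions are still open.

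At stake is selection after randomization. A per-protocol rule without a threshold is a judgement. If the arm is known, that judgement can favour one arm, even without intent. Data correction carries the same risk wherever a recorded value leaves room for interpretation.

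**Working it through.** The plan attaches no figure to this point, so there is none to reproduce. The check is the order of events, followed by one illustration of size.

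**Order of events**

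| Step | Source | Earliest time it can be complete |
|---|---|---|
| Last outcome assessment | Sections 2.1, 2.4; Table 1 | T4, week 12 |
| Allocation unsealed | Section 2.7 | End of outcome assessment |
| Source comparison, correction, logic and manual checks of T4 data | Section 2.8 | After T4 data are entered |
| Final drug count | Table 1 | T4 |
| Compliance and deviation judgement for the PPS | Section 2.10 | After the final drug count |

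The last three steps finish at or after the last assessment, which is also the unsealing event. No statement in the article places them before the unsealing. The article does not mention a database lock or a blind data review. That silence alone would be no finding in a condensed article. The point rests on the trigger that the article does state.

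**Where the exposure lies**

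- *FAS:* section 2.10 requires at least one dose and one recorded observation, and section 2.2.3 keeps withdrawn patients in the FAS. This needs little judgement.
- *Primary indicators:* HbA1c, fasting glucose, 2-hour glucose and triglycerides are laboratory values, and correction is against source documents. There is little room for bias.
- *PPS:* membership depends on a compliance judgement with no threshold. This is the most exposed step.
- *Symptom-based secondary outcomes:* the Seattle Angina Questionnaire and TCM symptom indicators leave more room at the correction stage than laboratory values do.

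**Worst-case illustration for the PPS**

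Input from the article: 100 patients per group (sections 2.1 and 2.9). Assumptions not in the article: no true effect, a normal outcome with SD 1, a two-sided test at 0.05, and removal of exactly the worst responders from the treated arm with allocation known.

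By hand, for five removed:
- Mean shift = φ(1.645)/0.95 = 0.1031/0.95 = 0.109 SD.
- Standard error of the difference = √(1/95 + 1/100) = 0.143 SD.
- Shift in standard errors = 0.109/0.143 = 0.76.
- Two-sided rejection = P(Z > 1.96 − 0.76) + P(Z < −1.96 − 0.76) = P(Z > 1.20) + P(Z < −2.72) ≈ 0.118.

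Simulation of 20,000 null trials with a t-test:

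| Worst treated patients removed | Rejection, two-sided | Rejection in favour of treatment |
|---|---|---|
| 0 | 5.2% | 2.6% |
| 1 | 6.0% | 4.1% |
| 2 | 7.0% | 5.7% |
| 3 | 8.8% | 7.7% |
| 5 | 13.4% | 12.9% |
| 10 | 30.6% | 30.5% |

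The hand figure is slightly below the simulated 13.4% because it holds the SD at 1, whereas trimming also lowers the SD of that arm.

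**The case against.** The strongest reply is that the harm needs correction and set selection to happen after unsealing, and no section says that they do. A lock and a blind review may be in the full protocol or the analysis plan, neither of which is shown. The first part stands: the article permits unblinded decisions and does not announce them. The second limits the point but does not remove it, because such a document would have to override a trigger that the article states.

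Two stronger readings are tempting, and the article supports neither.

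- A reader might infer that envelopes are opened patient by patient while recruitment continues. The wording of section 2.7 is collective, nothing describes one-by-one opening, and individual unblinding has its own route through the emergency letters.
- A reader might infer a contradiction with the statement in section 2.3 that "the treatment allocation remains blind throughout the study". If outcome assessment means that of the whole trial, allocation does stay blind until all outcomes are assessed. The article does not define the study as running to database lock, so no contradiction is shown.

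The illustration is also open to challenge. It assumes perfectly ranked removal from one arm, which amounts to deliberate selection, and it does not apply to the FAS. No section makes the PPS the primary analysis set. All of this stands.

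Section 2.10 assigns the analysis to an independent statistician, and section 2.1 keeps the funding company out of data collection and analysis. Both lower the risk. Neither says that those who correct data or decide set membership are blinded, and section 2.7 names only researchers and outcome assessors.

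**Conclusion.** The point holds in a limited form. Section 2.7 ends the blind at an event that comes before the T4 data can be fully corrected and before compliance through week 12 can be judged. Following the stated trigger therefore permits final corrections and PPS membership to be settled with treatment known.

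The practical size is modest. It is small for the laboratory primary indicators in the FAS and larger for the PPS and the symptom-based secondary outcomes. The simulated figures are an upper illustration of selective PPS exclusion, not an expected error rate for this trial. The conclusion assumes that outcome assessment means the assessment of all patients through T4, and that no document outside the article moves the trigger. The sentence should be corrected because the repair is cheap and it protects the double-blind claim.

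**What to change.** Replace the unsealing sentence in section 2.7 with:

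> *Envelopes stay sealed until all patients have completed T4, all queries are closed, FAS, PPS and safety-set membership is signed off blind, and the database is locked, except for emergency code-break of an individual patient.*

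Add that everyone who corrects data or decides analysis-set membership (the supervisor, the data coordination centre and the analysing statistician, as far as they have these tasks) remains blinded until then.

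The cost is a short delay to unblinding and a documented blind data review with sign-off of the three sets. Sample size, visits and measurements do not change.

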#### 2.2.3. Withdrawal, Dropout, and Discontinuation

Participation will be discontinued if the participant has sudden worsening of condition that is not confirmed to be associated with this trial, or serious adverse events, or is unable to cooperate with the trial investigators and/or to complete the follow-up. If the condition continues to worsen, complications or special physiological changes emerge, a participant refuses to continue the trial, or a participant uses medicines that are not permitted in this trial, the patient will be withdrawn from the trial after the researcher's assessment. The data will be considered invalid but will still be included in the full analysis set (FAS). Information from dropouts will be collected by phone interviews, such as the reason for the trial discontinuation and the status of the final medication received. Participants who withdraw from the trial will receive appropriate treatment for adverse events.

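### Section 2.7 excludes patients whose code is exposed without naming an analysis set; the only listed reasons for breaking the blind are outcome-related, and the rule contradicts 2.2.3 and 2.10

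*Protocol article*

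**What the plan says.** Three sections of the protocol article bear on a patient whose code is opened.

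- **2.7, Randomization and Blinding.** The rule is "If the blind code is exposed, patients will be excluded accordingly". The next sentence gives the reasons for opening a code: "Any of the following situations could call for a blind breaking and urgent measure: a serious adverse event, serious complication, or a deterioration". No other reason is listed, no reason is exempted from the exclusion, and no analysis set is named.
- **2.2.3, Withdrawal, Dropout, and Discontinuation.** Some of the same occurrences end participation, including serious adverse events and an abrupt decline in the patient's state. Continued worsening and complications also lead to withdrawal. On what happens to the data, the section says: "The data will be considered invalid but will still be included in the full analysis set (FAS"). Unblinding is not mentioned.
- **2.10, Statistical Analyses.** On the FAS: "In the FAS, patients will be dosed with the study drugs at least one time and one clinical observation will be recorded". On safety: "Subjects with safety data who have completed at least one study visit will be included in the safety analysis". The PPS requires good compliance and no protocol deviations. None of the three definitions refers to an exposed code.

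**The concern.** Every listed reason for breaking the blind arises after randomisation and reflects how the patient is doing. If a broken code leads to exclusion, whether a randomised patient is analysed depends on outcome, and possibly on treatment as well. The two groups that remain are then no longer the groups that were randomised.

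The results most exposed are those for which unblinded patients supply the information: serious adverse events, hemorrhage, and the monitored clinical events (cardiac death, nonfatal myocardial infarction, coronary revascularization). The angina scores come next. A handful of patients can decide a comparison of rare events.

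There is a second difficulty. An unblinded patient with a serious adverse event is excluded under 2.7 but retained under 2.2.3 and 2.10, and nothing says which rule governs. If that is settled after codes have been opened, whoever decides may know both the patient's arm and the patient's outcome.

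**Working it through.** **No planned figure to reproduce.** The point concerns a rule, and the document gives no rate of unblinding or of serious events. The first check is therefore to follow one patient through the text.

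**Step 1. One patient, three sections.** Take a patient who is dosed, has one clinical observation and safety data from a completed visit, then has a serious adverse event and is unblinded.

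| Section | Treatment of this patient |
|---|---|
| 2.7 | Excluded, from a set not named |
| 2.2.3 | Participation ends; data called invalid but kept in the FAS (assuming that sentence covers discontinued as well as withdrawn patients) |
| 2.10, FAS | Included: one dose and one observation |
| 2.10, safety | Included: safety data and one visit |
| 2.10, PPS | Not settled: an exposed code is not mentioned |

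These entries agree only if the exclusion in 2.7 means the PPS, or means further participation. The text says neither.

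**Step 2. Event rates if the exclusion reached the FAS or safety set.** Input from the document: 100 patients per group. Assumed: 10 patients with a serious event in each group, so no true difference. With e event patients excluded, the observed rate is (10 − e)/(100 − e).

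- 5 treated and 2 control excluded: 5/95 = 5.3% against 8/98 = 8.2%.
- 8 treated and 4 control excluded: 2/92 = 2.2% against 6/96 = 6.3%.
- 5 excluded in each group: 5/95 = 5.3% in both, against a true 10%.

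Unequal exclusion creates a difference where none exists, and swapping the groups reverses its sign. Equal exclusion leaves no spurious difference here but understates both rates.

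**Step 3. A continuous outcome.** All inputs are assumptions. The outcome Y has SD 1 in each group, higher is worse, and the true effect is −0.45 SD. A deterioration score with SD 1 has correlation ρ with Y, and patients above a common cut-off c are excluded. In a group with mean μ, put a = c − ρμ. The excluded fraction is 1 − Φ(a), and the mean of those retained is μ − ρ·φ(a)/Φ(a).

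| ρ | Control excluded | Treated excluded | Retained effect (SD) |
|---|---|---|---|
| 0.2 | 2% | 1.6% | −0.448 |
| 0.3 | 5% | 3.8% | −0.443 |
| 0.7 | 2% | 0.9% | −0.433 |
| 0.7 | 5% | 2.5% | −0.416 |
| 0.7 | 10% | 5.5% | −0.396 |

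The last row in full: c = 1.282. The control mean falls by 0.7 × 0.1755/0.90 = 0.137 and the treated mean by 0.083, so the effect is −0.45 − 0.083 + 0.137 = −0.396.

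**Step 4. The other direction.** Keep ρ = 0.7 but let unblinding be commoner on the drug, with 5% of treated and 2.5% of control patients excluded. The treated mean falls by 0.7 × 0.1031/0.95 = 0.076 and the control mean by 0.7 × 0.0584/0.975 = 0.042. The effect becomes −0.45 − 0.076 + 0.042 = −0.484, which flatters the drug.

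**The case against.** The strongest reply is that the definitions in 2.10 already govern. An unblinded patient with one dose and one observation meets the FAS definition, and one with safety data and a completed visit meets the safety definition. Section 2.2.3 keeps patients withdrawn for much the same reasons in the FAS. On that reading, the exclusion in 2.7 means leaving the trial or leaving the PPS, and nothing is lost. This is a condensed article, and a fuller document may say so.

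Part of this stands. A reader might infer that the trial discards its worst outcomes, or that every unblinded serious adverse event vanishes from the safety analysis. The documents do not support either. The listed events only could call for breaking the blind, so at most the unblinded subset is affected. The only rule for the safety set would, on its face, keep those patients. Section 2.5 also requires adverse events to be recorded and severe ones reported, whatever happens to the code.

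It is also fair to say that the larger shifts in the continuous illustration need a correlation of 0.7 between deterioration and outcome. The document gives no support for that where the outcome is HbA1c, fasting glucose, 2-hour glucose or triglycerides.

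What does not stand is the idea that this is only detail left out for brevity. The article states an exclusion, without limits, directly beside a list of outcome-related triggers. The benign reading has to be supplied by the reader, and it requires 2.7 to mean something it does not say.

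**Conclusion.** The concern holds in this form: 2.7 states an unrestricted exclusion of patients whose code is exposed, the only listed reasons for opening a code are outcome-related, and the rule contradicts 2.2.3 and the FAS and safety definitions in 2.10. Whether harm follows depends on which section is applied, and the document does not decide that.

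If the exclusion reached the FAS or safety set, serious and clinical-event rates would be understated, and the comparison could be distorted either way. With assumed counts of 10 events per 100 in each group, unequal exclusion produces gaps such as 5.3% against 8.2%. For a continuous outcome with an assumed effect of 0.45 SD, the retained effect lies between about 0.44 and 0.45 SD at correlations of 0.2 to 0.3 with 2% to 5% of controls excluded. It falls to about 0.40 SD at a correlation of 0.7 with 10% and 5.5% excluded, and rises to about 0.48 SD when unblinding is commoner on the drug. None of these rates or correlations comes from the protocol. The effect on the four laboratory primary indicators is probably small; safety, clinical-event and angina results are more exposed.

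**What to change.** Replace the exclusion sentence in 2.7 with wording to this effect: patients whose code is broken remain in the FAS, analysed in the group to which they were randomised, and in the safety set, analysed by treatment received; the date and reason for each code break are recorded; such patients may be left out of the PPS at most.

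Then align the other two sections. In 2.2.3, reconcile calling the data invalid with keeping them in the FAS, and say whether that sentence covers discontinued as well as withdrawn patients. In 2.10, state that an exposed code does not remove a patient from the FAS or safety set, and whether it removes a patient from the PPS.

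The change concerns analysis sets only and leaves the reasons for breaking the blind as they are. It costs one replaced sentence and two short alignments, with no extra patients; the only data item is the date and reason for each code break. It should be settled before any code is opened for analysis.

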### 2.8. Data Entry and Quality Control

The data of the participants collected according to the Case Report Forms will be imported into the clinical data management system (http://www.xyedc.com/). To keep the data consistency, the supervisor will compare the electronic database with the source documents and correct any identified errors. In addition, computer logic checks will be run after data entry. Manual checks and the Data Coordination Center will also help to identify more complicated and less common errors. All these measures are used to ensure the accuracy and integrity of information.

### 2.9. Sample Size Calculation

The sample size was determined with a type I error rate of *α* = 0.05 and a power of 80% (type II error rate of *β* = 0.2). According to a previous study, the efficacy rate of Zhenyuan capsules is 94% for relieving angina pectoris symptoms and 64% for placebo [10]. The sample size should therefore consist of 25 participants in each group. Considering the potential 20% loss and the cases that can be counted in each center, 100 participants are needed for each group. As treatment and control groups, and three centers are involved, 200 participants will be recruited in this study. The formula used to calculate the sample size is as follows:(1)$$\begin{array}{c} n=\frac{p_{1}\left(1-p_{1}\right)+p_{2}\left(1-p_{2}\right)}{{\left(p_{1}-p_{2}\right)}^{2}}{\left(\;u_{1-\alpha }+u_{1-\beta }\;\right)}^{2}, \end{array}$$*n* ≈ 25 patients/group.

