### 2.4. Outcomes and Measures

The primary indicators, HbA1c, fasting blood glucose (FBG), 2-hour postprandial blood glucose (2hPBG), and triglyceride (TG) levels, will be tested at T0, T1, T2, T3, and T4. The secondary indicators, ultrasonic cardiography (UCG) finding, coagulation indicator, and P- selectin level, will be assessed at T1 and T4. Cardiac death, nonfatal myocardial infarction, coronary revascularization, Seattle Angina Questionnaire (SAQ) score, and TCM symptom indicators will also be monitored periodically. Adverse events, which include hemorrhage, will be followed up using electrocardiography, routine urinalysis, routine stool test, and liver and kidney function tests (ALT, AST, Cr, and BUN) from T1 to T4. Items to be measured and the time window of data collection are shown in Table 1.

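### The only power statement is for an angina-relief rate, so the stated 80% power applies to none of the four primary indicators

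*Protocol article*

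**What the plan says.** Section 2.9 (Sample Size Calculation) sets "a type I error rate of *α* = 0.05 and a power of 80" percent. Its effect assumption is that "the efficacy rate of Zhenyuan capsules is 94% for relieving angina pectoris symptoms and 64% for placebo", taken from a previous study. It prints an unpooled two-proportion formula and concludes: "The sample size should therefore consist of 25 participants in each group". It then moves to the final number: "Considering the potential 20% loss and the cases that can be counted in each center, 100 participants are needed for each group". The total is 200.

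Section 2.4 (Outcomes and Measures) defines the primary outcomes: "The primary indicators, HbA1c, fasting blood glucose (FBG), 2-hour postprandial blood glucose (2hPBG), and triglyceride (TG) levels, will be tested at" T0 to T4. The abstract names the same four. Section 2.10 summarises continuous variables as mean ± SD.

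Angina has a lesser place. The Seattle Angina Questionnaire is secondary in the abstract and is listed for periodic monitoring in section 2.4. Table 1 lists angina pectoris scores among the efficacy observations. A rate of angina relief is not defined as an outcome in section 2.4.

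**The concern.** A power figure belongs to one endpoint, one effect size and one test. Here the endpoint is binary relief of angina symptoms, the effect is 30 percentage points, and the test compares two proportions. The trial will be judged on four continuous laboratory values. Nothing in the article gives a difference, SD or responder rate for any of them, or links angina relief to glucose or triglyceride change. The Discussion describes this as the first use of the capsule in blood lipid research, so an angina result from earlier work cannot stand in for a triglyceride effect.

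What is at stake is how the result is read. A null finding on HbA1c or triglycerides would be taken to come from a trial with 80% power, although no such power was shown. Nor can a reader tell what size of glucose or lipid effect the trial could detect.

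**Working it through.** **Inputs from section 2.9:** p1 = 0.94, p2 = 0.64, α = 0.05, power 0.80, 20% loss, 100 per group. Allocation is 1:1 (section 2.7). Effect sizes and SDs for the primary indicators are not given, so the standardised differences below are assumptions.

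**1. Reproducing the plan's 25 per group**

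n = [p1(1 − p1) + p2(1 − p2)] / (p1 − p2)² × (u + 0.8416)²

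- Numerator: 0.94 × 0.06 + 0.64 × 0.36 = 0.0564 + 0.2304 = 0.2868.
- Divided by 0.30² = 0.09: 3.187.
- With the two-sided u = 1.960: 3.187 × 7.849 = 25.01. This matches the stated 25.
- With u read literally as one-sided, 1.645: 19.7, which does not match.

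The 80% is therefore the power of a two-sided comparison of angina-relief rates at 25 per group. The printed subscript 1 − α looks like a notation slip and does not affect this point.

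**2. From 25 to 100 per group**

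Allowing for 20% loss: 25 / 0.80 = 31.25, rounded up to 32. The rest of the step, from 32 to 100, rests on the number of cases per centre, which is not quantified. The final 200 is not formally derived for any endpoint.

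**3. Power for angina relief at the actual size**

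With 80 evaluable per arm (100 × 0.80), unpooled: z = 0.30 / √(0.2868 / 80) = 5.01, and Φ(5.01 − 1.96) = 0.999. The pooled version gives 99.8%. So even for angina relief, 80% does not describe the trial as sized.

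**4. What the actual size gives for one continuous primary indicator**

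Two-sided unadjusted t-test, non-central t distribution:

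| Per arm | α | Difference detectable with 80% power | Power at 0.30 SD |
|---|---|---|---|
| 80 | 0.05 | 0.446 SD | 47% |
| 80 | 0.0125 | 0.533 SD | 27% |
| 100 | 0.05 | 0.398 SD | 56% |

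The 0.0125 row is 0.05 / 4. It is illustrative only: section 2.10 applies P < 0.05 to every analysis and states no split.

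Over assumed differences of 0.2 to 0.5 SD, with 80 to 100 per arm at α = 0.05, power runs from 24% to 94%. The document gives no basis for choosing a point in that range.

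**5. In HbA1c units**

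This needs an assumed week-12 SD. At 0.5 to 0.8 percentage points, 0.446 SD is 0.446 × 0.5 = 0.22 to 0.446 × 0.8 = 0.36 points. Eligibility restricts HbA1c to 5.7–7%, and a uniform spread over that range has SD 1.3 / √12 = 0.38, which would give 0.446 × 0.38 = 0.17 points.

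**The case against.** The strongest reply is that no harm has been shown. The recruited number is four times what the formula requires, and 80 to 100 per arm detects about 0.45 to 0.40 SD, which may be adequate. The 0.30 SD used above is the reviewer's choice. Section 2.10 also plans analysis of covariance. If the baseline value were a covariate with correlation 0.5 to 0.7 to the outcome (an assumption; the article names no covariates), the detectable difference would fall to 0.446 × √(1 − 0.5²) = 0.39 SD or 0.446 × √(1 − 0.7²) = 0.32 SD. Power at 0.30 SD would rise from 47% to about 59–75%. Angina is also not absent from the trial, since the questionnaire and the angina scores are collected.

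Much of this stands. Underpowering is not established, the unadjusted figures are conservative if a strong baseline covariate is used, and only the 25 per group, not the final 200, comes from the angina rate. None of it attaches the 80% to a primary indicator. Each of these arguments supplies an effect size, SD or correlation that section 2.9 does not contain.

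It could also be said that such detail belongs in an analysis plan that is not shown. But section 2.9 does give a power justification, and gives it for the wrong endpoint. That is a conflict between two explicit statements, not an omission.

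**Conclusion.** The point holds and must be fixed. The article's only power claim describes a 94% versus 64% angina-relief comparison at 25 per group. For HbA1c, fasting glucose, 2-hour postprandial glucose and triglycerides, power is undetermined, and the recruited 100 per group has no stated power basis for any of them.

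The detectable difference of 0.45 SD rests on 20% loss, a two-sided unadjusted test at 0.05 and one indicator taken alone; covariate adjustment would lower it and a multiplicity split would raise it. The mismatch itself depends on none of these assumptions. The finding is not that 200 patients are too few.

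**What to change.** Keep 200 patients and rewrite section 2.9. Suggested wording: *The sample of 200 (100 per arm) is set by feasibility across three centres. After 20% loss, 80 per arm give 80% power at two-sided 0.05 to detect a standardised difference of 0.45 SD at week 12 in HbA1c; the same standardised figure applies to fasting glucose, 2-hour postprandial glucose and triglycerides, each taken alone.*

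Then:

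- Give each standardised difference in clinical units, with a sourced SD, and say whether an effect of that size is plausible and worthwhile. Without this, the statement is only a back-calculation.
- If α is divided over the four indicators, give the matching figure (0.53 SD at 0.0125). If covariance adjustment is relied on, state the assumed correlation.
- Move the 94% versus 64% calculation to a supportive remark on angina symptoms, and show the two-sided quantile in the formula.

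The cost is a rewording of section 2.9 and a less favourable stated power. Recruitment and conduct do not change.
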